### Data collection and data management

Demographic details (age, gender, race/ethnicity, marital status, district/county of residence, and insurance), clinical data (CRFs), laboratory data (whole blood count, comprehensive metabolic panel, INR, fasting lipid panel, HbA1C, and AFP), imaging details (ultrasound, Fibroscan [or ARFI], MRI, ECG), biospecimen for storage (plasma, urine, and if feasible, tissue), and other data specified in Table 1 will be collected from each patient.

Patient-reported data will be extracted from the hospital information systems or collected based on a structured form and will be uploaded to a central database using a pre-formatted data structure. Experienced, skilled, locally licensed radiologists from the study sites in Vietnam and Saudi Arabia will read the MRI results and interpret the findings. Additionally, an independent radiologist with similar practicing experience will re-read the MRI and validate the interpretations. Trained and experienced research staff will handle data collection and management. Data will be stored in a secure setting to maintain privacy. The data monitoring committee will be comprised of the Principal Investigators, Data Management Co-Investigator, Overall Study Manager and Vietnam Study Manager, Saudi Arabia Study Manager, and Biostatistician.

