Early detection in asymptomatic patients is a strategy to improve survival outcomes in HCC management. GALAD score is a serum biomarker-based panel that can improve early HCC detection in patients with chronic liver disease, including liver fibrosis and cirrhosis. In this protocol, GALAD will combine gender and age with the results from alpha-fetoprotein (AFP), lens culinaris agglutinin (LCA) bound fraction of AFP (AFP-L3%), and protein induced by vitamin K absence-II (PIVKA-II) or des-gamma-carboxy-prothrombin (DCP) levels. This score has been internally and externally validated [8] and recently received breakthrough designation from the United States Food and Drug Administration (US FDA). The performance of GALAD has been evaluated as a surveillance test for HCC in the United States, United Kingdom, Germany, Japan, and Hong Kong in case–control studies as well as in studies with design as PROBE (prospective specimen collection and retrospective blinded evaluation) [9]. However, it has not yet been evaluated in Vietnam or Saudi Arabia [8]. And most importantly, GALAD has not been investigated and validated prospectively for clinical surveillance of HCC in which GALAD score is applied to individuals in real-time and diagnostic procedures are performed for those with an elevated GALAD test (≥ -0.63).

In order to provide robust data for the potential use of GALAD in Vietnam and Saudi and as the next step in GALAD score biomarker development [10], we propose to conduct a phase IV biomarker validation study to prospectively survey a cohort of patients at risk for HCC (i.e., patients with advanced fibrosis or compensated cirrhosis and irrespective of cirrhosis etiologies), using semi-annual abdominal ultrasound and GALAD Score for five years. In doing so, we aim to validate the potential role of GALAD Score for clinical surveillance and early detection of HCC in Vietnam and Saudi Arabia. Additionally, we will collect and archive biospecimens to promote future research in chronic liver disease in Vietnam and Saudi Arabia.

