### Outcome measures

The primary endpoint is the performance of GALAD score determined in association with HCC detection by LiRADS criteria in a cohort with advanced fibrosis or cirrhosis (e.g., Metavir F3 or higher, with MELD 15 or lower) undergoing prospective surveillance every six months for five years. Performance of GALAD score will be determined by using the GALAD score cut-off value of -0.63 to prospectively survey a cohort of 1,600 patients with advanced fibrosis and early cirrhosis (e.g., Metavir F3 or higher, with MELD 15 or lower) for early detection of HCC by Liver Imaging Reporting and Data System (LiRADS) assessment (LiRADS-5). The GALAD cut-off value was previously determined in case–control studies [11]. For the establishment of the biorepository, the endpoint is the proportion of study participants who agree to consent for bio-specimen when invited.

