### Study schedule and assessments

Figure 2 depicts the study schema. The study is planned for five years. Individuals with a liver mass ≥ 1 cm in diameter, elevated AFP (≥ 9 ng/mL), and/or elevated GALAD score (≥ -0.63) will be scanned with dynamic contrast-enhanced MRI, and a diagnosis of HCC will be made by LiRADS-5. Additionally, those who do not exhibit abnormal imaging findings, elevated AFP titer, and/or elevated GALAD score will obtain a dynamic contrast-enhanced MRI annually for five years to assess for HCC. In Vietnam, the study sites and the funds to be received for the study will be used for conducting all the tests and MRIs. National health insurance will not be used. In Saudi Arabia, national health insurance will cover the participants’ tests and MRIs.

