**Fig. 2 Fig2:**
[figure not shown]
Study Schema. Patients with chronic liver diseases from hospital database of the participating sites will be screened and invited for enrollment if eligible. Next, we prospectively survey the eligible cohort of patients at risk for HCC (i.e. patients with advanced fibrosis or compensated cirrhosis and irrespective of cirrhosis etiologies), using semi-annual abdominal ultrasound and GALAD Score for five years. During the 5-year follow-up, individuals with a liver mass ≥ 1 cm in diameter and/or elevated GALAD score (≥ -0.63) will be scanned with dynamic contrast-enhanced MR,I and a diagnosis of HCC will be made by LiRADS assessment (LiRADS-5). Additionally, those who do not exhibit abnormal imaging findings and/or elevated GALAD score will obtain a dynamic contrast-enhanced MRI annually for five years to assess for HCC

During the 5-year time frame, we anticipate at least 80 (approximately 16 each year if 1% incidence x five years for both cohorts in Vietnam and Saudi Arabia) or as many as 320 (64 per year if 4% incidence x five years for both cohorts in Vietnam and Saudi Arabia) incident HCC cases given the high HCC incidence rate in Vietnam and Saudi Arabia. With the range of 80 to 320 anticipated HCC cases, we will have 90% to 99% power, respectively, to detect a meaningful difference in the cases vs. control (more on sample size calculation below). We will compare sensitivity for early HCC detection (primary outcome measures), false-positive results, and resultant diagnostic evaluation.

By leveraging the prospective cohort, we will establish a biorepository of longitudinally collected biospecimens from patients with fibrosis/cirrhosis to be used as a reference set for future research. Clinical, laboratory, and imaging data, urine, and plasma biospecimens are from participants for up to five years; data are collected only from participants who maintain the absence of evidence of HCC on imaging and/or biopsy. Biospecimens and associated de-identified clinical data from participants enrolled in this study will be stored in Vietnam for participants from Vietnam and in Saudi Arabia for participants enrolled from Saudi Arabia.

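### The described MRI reading masks neither radiologist to GALAD and names no deciding read, so the index test can influence its own LiRADS-5 reference standard

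*Protocol article*

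**What the plan says.** Under Outcome measures, the protocol article states: "The primary endpoint is the performance of GALAD score determined in association with HCC detection by LiRADS criteria". Whoever assigns LiRADS-5 therefore sets the reference standard.

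The Background presents the study as the first prospective use in which "GALAD score is applied to individuals in real-time and diagnostic procedures are performed for those with an elevated GALAD test". Study schedule and assessments lists three triggers: a liver mass of at least 1 cm, AFP of at least 9 ng/mL, or GALAD of at least -0.63. Participants with any of these "will be scanned with dynamic contrast-enhanced MRI, and a diagnosis of HCC will be made by LiRADS-5". Those without a trigger "will obtain a dynamic contrast-enhanced MRI annually for five years to assess for HCC".

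The reading is described under Data collection and data management. There, "locally licensed radiologists from the study sites in Vietnam and Saudi Arabia will read the MRI results and interpret the findings", and then "an independent radiologist with similar practicing experience will re-read the MRI and validate the interpretations". Outcome ascertainment and study exit definitions also accepts HCC confirmed on biopsy, and ends study participation once HCC develops.

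**The concern.** In a diagnostic accuracy study the reference standard should be assigned without knowledge of the index test. Here the index test is known when the scan is ordered and can be the reason for ordering it. LiRADS-5 has set criteria, but a reader still applies them. The doubtful cases tend to be small or atypical nodules, on which a claim of early detection depends.

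If a borderline nodule is read up to LiRADS-5 because GALAD is positive, a GALAD false positive becomes a true positive. If a nodule is left below LiRADS-5 because GALAD is negative, a false negative becomes a true negative. Both shifts raise apparent sensitivity and apparent specificity. The planned bootstrap intervals describe sampling variation and would not reveal this bias.

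The Discussion makes the risk concrete. It reports that in Vietnam the main local use of AFP, AFP-L3% and DCP assays is to help stratify HCC risk when a nodule looks atypical on cross-sectional imaging. These are GALAD's serum components. By the article's own account, clinicians in one of the two countries already bring them to bear on doubtful nodules.

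**Working it through.** **1. Is masking stated anywhere?** The sections on MRI triggering, MRI reading, outcome ascertainment and analysis (Background, Outcome measures, Study schedule and assessments, Screening, Table 1, Follow-up visits, GALAD score, Outcome ascertainment, Data collection, Statistical methods) were read for it. None masks either reader to GALAD, AFP, ultrasound or the reason for the scan. None masks the second reader to the first, and none says how disagreement is settled. The only mention of blinded evaluation, in the Background, describes earlier retrospective studies. Equally, no section says that readers are given the GALAD result.

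**2. Could a reader infer a positive GALAD?** Partly. Table 1 schedules contrast CT or MRI at Visits 1, 3, 5, 7 and 10. A contrast scan at Visit 2, 4, 6, 8 or 9 therefore suggests a trigger. If ultrasound showed no mass, AFP or GALAD remains, and AFP is itself a term in the GALAD formula. At Visits 3, 5, 7 and 10, which are 4 of the 9 follow-up visits, a triggered scan coincides with a routine one and reveals nothing by its timing.

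**3. Size under assumed lesion counts.** The plan gives no figure to reproduce. The case numbers come from the text under the Fig. 2 legend: "With the range of 80 to 320 anticipated HCC cases". Everything else is an assumption: true sensitivity 60%, *a* borderline GALAD-positive non-HCC lesions read up to LiRADS-5, and *b* GALAD-negative HCCs read below it.

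Apparent sensitivity = (TP + a) / (TP + a + FN − b)

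With 80 cases, TP = 48 and FN = 32. With 320 cases, TP = 192 and FN = 128.

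| a | b | 80 cases | 320 cases |
|---|---|---|---|
| 0 | 0 | 48/80 = 60.0% | 192/320 = 60.0% |
| 5 | 0 | 53/85 = 62.4% | 197/325 = 60.6% |
| 5 | 3 | 53/82 = 64.6% | 197/322 = 61.2% |
| 10 | 5 | 58/85 = 68.2% | 202/325 = 62.2% |

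**4. Size under assumed misreading rates.** Let *u* be the share of GALAD false positives read up and *d* the share of GALAD-negative HCCs read down. The calculation is at patient level with 1,600 participants and an assumed specificity of 0.85 to 0.95.

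Apparent sensitivity = (TP + u·FP) / (TP + u·FP + FN·(1 − d))

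Worked example with 80 cases, sensitivity 0.70, specificity 0.85, u = 0.10 and d = 0.20: TP = 56, FN = 24, FP = 1,520 × 0.15 = 228. Then (56 + 22.8) / (56 + 22.8 + 19.2) = 78.8/98.0 = 0.804.

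| Assumed true sensitivity | Misreading | 80 cases | 320 cases |
|---|---|---|---|
| 0.70 | u = 0.01, d = 0 | 0.703–0.708 | 0.701–0.702 |
| 0.70 | u = 0.10, d = 0.20 | 0.768–0.804 | 0.750–0.760 |
| 0.50 | u = 0.01, d = 0 | 0.505–0.514 | 0.501–0.503 |
| 0.50 | u = 0.10, d = 0.20 | 0.598–0.662 | 0.565–0.583 |

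The direction is the same throughout because the assumed misreading follows the GALAD result. The size runs from negligible to about 16 percentage points (0.662 − 0.500 = 0.162) and depends wholly on the assumed rates.

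**The case against.** The strongest objection is that this is silence in a condensed article. Reader masking and adjudication are often placed in a full protocol or imaging manual, which is not shown. It stands to this extent: a reader might infer that the radiologists are known to be unmasked, and the text does not say so. It does not dispose of the point. The article itself sets out the reading process, including who reads, their experience and what the second reader does, and the task it gives the second reader is to validate the interpretations.

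Other objections limit how far the point reaches:

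- **Deciding read.** A reader might infer that the local read is the diagnosis. The article names no deciding read, and it also accepts biopsy.
- **Second reader.** A reader might infer that the second radiologist merely endorses the first. The same sentence says that this radiologist is independent and re-reads the images. What is missing is masking and a rule for disagreement.
- **Triggers.** GALAD is one of three, and everyone has scheduled MRI. A scan alone does not reveal a positive GALAD, and annual MRI in untriggered participants limits differential verification. This reduces the risk without removing it.
- **Ultrasound.** A reader might infer that ultrasound is put at a disadvantage. An unmasked reader could also know that ultrasound had shown a mass, which would favour ultrasound by the same route. The net effect on that comparison is undetermined.
- **Masked MRI as sole reference.** This would class a biopsy-proven HCC below LiRADS-5 as a non-case. It would also leave truncated follow-up in participants who exited on a local diagnosis that the masked read did not confirm. Both are fair, and the remedy must deal with them.

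**Conclusion.** The point holds as a weakness in the reading process as described. GALAD is known in real time and can trigger the scan that sets its own reference standard. The stated process contains neither masking nor a rule for the deciding read. Review bias is a realistic risk and would most likely favour GALAD on the primary endpoint.

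Its size cannot be estimated from the documents. The figures above show only what particular assumed misreadings would do, and they should not be read as expected bias. The conclusion assumes that no unseen document already specifies masking; if one does, stating it in the protocol settles the matter. No change in sample size follows.

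The change is worth making because the second read is already planned, and masking it is plainly better than an unmasked validation. It is best made before reads accumulate, since Statistical methods plans to re-evaluate the -0.63 cut-off after year 2.

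**What to change.** In Data collection and data management:

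1. Have the independent radiologist read each MRI masked to the local read, GALAD, AFP, ultrasound and the reason for the scan (scheduled or triggered).
2. Record that reader's LiRADS category before any discussion.
3. Use the masked read, together with biopsy confirmation where available, as the reference standard for the performance analysis.
4. State that the local read continues to guide care.
5. Report agreement between the two reads.
6. Add a sensitivity analysis using the local diagnosis. It should cover participants who left follow-up on a local HCC diagnosis that the masked read did not confirm.

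No extra scan or reader is needed. The costs are de-identified image handling with the request text removed, one case report form field and the protocol wording. Some research classifications will differ from the clinical diagnosis; items 5 and 6 make those differences visible.

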### Missing data

The missing data and data of those who lost to follow-up will be analyzed and reported in two ways. One is that we will treat them as incomplete data, remove them from the analyses, and only report the results of those who have completed data. The second way is to impute the data as complete cases based on other cases with complete data, subject them to sensitivity analysis, and subsequently report them as complete data.

When we calculated the sample size for the study, we accounted for up to 30% missing data or loss to follow up.

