### Sample size

Two estimates were calculated for the sample size, assuming low (1%) and high (4%) annual incidence rates in the population with the highest risk for HCC. Assuming an annual incidence of 1%, 90% power and alpha of 0.05 during the 5-year follow-up period, we anticipate a 5-year incidence proportion of 0.05 (5*0.01). The sample size needed is 621 (each country). For a 4% annual incidence rate using the same assumptions, the sample size required is 119. To err on the conservative side, we aimed to recruit 800 per country (Vietnam and Saudi Arabia) to account for the loss to follow-up. These sample size calculations were performed in Stata 15.1 using the “sampsi” command.

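### The stated allowance for up to 30% loss is not fully covered: 800 per country absorbs about 22%, and 30% loss leaves 560 against the required 621

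*Protocol article*

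**What the plan says.** Two sections of the protocol article bear on this.

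- **Missing data:** "When we calculated the sample size for the study, we accounted for up to 30% missing data or loss to follow up". The same section plans two analyses, one that removes incomplete cases and one that imputes them.
- **Sample size:** for the low-incidence case, the inputs are "Assuming an annual incidence of 1%, 90% power and alpha of 0.05 during the 5-year follow-up period", and "we anticipate a 5-year incidence proportion of 0.05 (5*0.01"). The result is "The sample size needed is 621 (each country"). For the high-incidence case, "For a 4% annual incidence rate using the same assumptions, the sample size required is 119". The target is then set: "To err on the conservative side, we aimed to recruit 800 per country (Vietnam and Saudi Arabia) to account for the loss to follow-up". No loss percentage is given in this section. The routine named is Stata's sampsi.

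The text under Study schedule and assessments (after the Fig. 2 legend) gives an anticipated range of 80 to 320 incident cases over five years and links it to 90% to 99% power.

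**The concern.** The article states all three numbers needed to check the claim: the requirement (621), the target (800) and the allowance (30%). Together they fail. The step from 621 to 800 is the only place where loss enters the calculation, and it is too small for the percentage claimed.

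At stake is a statement of robustness. A reader would take it that 90% power survives 30% loss even at the lower incidence. In the complete-case analysis it does not. The 1% scenario is the one that matters here, because the target is described as conservative and 621 is the larger of the two requirements.

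**Working it through.** **Inputs.** Required number 621 per country at 1% per year and 119 at 4% per year; target 800 per country; 90% power; alpha 0.05; five-year proportion 0.05 (all Sample size). Allowance up to 30% (Missing data). The five-year proportion at 4% is 5 × 0.04 = 0.20. The comparison proportion and the sidedness of the test are not stated.

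**Step 1: reproduce the plan's figures.** The two-sample formula for proportions, two-sided, is

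n′ = [1.960·√(2p̄(1−p̄)) + 1.282·√(p₁(1−p₁) + p₂(1−p₂))]² / d², with d = |p₁ − p₂|,

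and with continuity correction n = (n′/4)·[1 + √(1 + 4/(n′d))]².

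| Comparison | Without correction | With correction | Article |
|---|---|---|---|
| 5% vs 10% | 582 | 620.4, so 621 | 621 |
| 20% vs 40% | 109 | 118.02, so 119 | 119 |

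A doubling of the five-year proportion reproduces both published figures. It is an inference from that match, not something the article says. It also shows that 621 is the raw output of the formula, with no loss allowance already inside it.

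**Step 2: test the 30% allowance.** This step does not depend on the inferred comparison.

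- Retained at 30% loss: 800 × 0.70 = 560, and 621 − 560 = 61 short (9.8% of 621).
- Number needed to retain 621: 621 / 0.70 = 887.1, so 888.
- Largest loss that 800 absorbs: 1 − 621/800 = 22.4%.

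Two more lenient calculations do not rescue the claim. Multiplying instead of dividing gives 621 × 1.30 = 807.3, so 808, still above 800. Dropping the continuity correction gives 582 / 0.70 = 831.4, so 832.

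**Step 3: the 4% scenario.** 119 / 0.70 = 170. The target of 800 is ample.

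**Step 4: power at 560 (conditional on 5% vs 10%, with 560 in each group of the comparison).**

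Power = Φ{[d√n′ − 1.960·√(2p̄(1−p̄))] / √(p₁(1−p₁) + p₂(1−p₂))}, where 1.960·√(2 × 0.075 × 0.925) = 0.730 and √(0.0475 + 0.09) = 0.371.

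- Without correction, n′ = 560: (0.05 × 23.66 − 0.730)/0.371 = 1.22, power 88.9%.
- With correction, n′ = (560 × 0.05 − 1)² / (560 × 0.05²) = 729/1.4 = 520.7: (0.05 × 22.82 − 0.730)/0.371 = 1.11, power 86.6%.

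On the corrected basis, 621 gives 90.0%, as it should.

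**Step 5: the anticipated case range (secondary).** The article's range is 1,600 × 0.01 × 5 = 80 and 1,600 × 0.04 × 5 = 320, with no loss. Assume loss at a constant rate reaching 30% at five years: λ = −ln(0.70)/5 = 0.0713 per year. Expected cases at 1% are then 1,600 × [0.01/(0.01 + λ)] × [1 − exp(−5(0.01 + λ))] = 65.7. The same model without loss gives 1,600 × [1 − exp(−0.05)] = 78.0. Loss therefore accounts for about 12 cases.

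**The case against.** The strongest reply is that the target was raised for loss, and the article says so: "we aimed to recruit 800 per country (Vietnam and Saudi Arabia) to account for the loss to follow-up". This stands. A reader might infer from the mismatch that no allowance was made at all; the documents do not support that. The step from 621 to 800 is an allowance of about 22%. The ratio 800/621 = 1.288 would fit 621 × 1.30 rounded down, although the article does not show how 800 was reached.

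Second, 560 is a worst case. It treats everyone with missing data or early loss as contributing nothing. That matches only the first of the two planned analyses; the second imputes, and the time-to-event analyses count person-time up to loss. This also stands, so the power figures above apply to the complete-case analysis only.

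Third, 5% versus 10% is not in the article. That is correct, and the 87% and 89% must carry that label. The shortfall of 560 against 621 does not depend on it.

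Fourth, the case range is stated as incidence times five years and does not claim to include loss. So it does not contradict the Missing data section. A reader might set 80 against 66 and put the whole gap down to loss, but that mixes the article's linear count with an exponential model. The like-for-like contrast is 78 against 66, and it rests on an assumed loss pattern.

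Finally, the effect is small and confined to one scenario. That limits the weight of the point but does not make the 30% statement correct.

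**Conclusion.** The point holds: the stated allowance of up to 30% is not fully covered by the stated sample size. On the article's own figures, 800 per country tolerates at most 22.4% loss; at 30% it leaves 560, and keeping 621 would take 888. No other statement in the article reconciles these numbers.

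The consequence is modest. It arises only at 1% annual incidence and only if loss exceeds about 22%. If the unstated comparison is a doubling, complete-case power at the full 30% is about 87% with continuity correction, or 89% without, against the stated 90%. A reader might infer that the study is materially underpowered or must enrol more patients; a drop of about three points in one scenario does not support that. This is a wrong statement that should be corrected, not a flaw in the design.

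**What to change.** Make one of two changes:

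1. In Missing data, say that the sample size allows for up to about 22% missing data or loss to follow-up; or
2. Keep 30% there, and add to Sample size that at this loss complete-case power in the 1% per year scenario is about 87%, naming the comparison assumed (5% versus 10%, if the study team confirms it).

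Either way, it helps to say that the 4% scenario is unaffected.

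Optionally, note under Study schedule and assessments that the range of 80 to 320 cases assumes no loss. If a figure is wanted, give about 66 for the low end, against 78 under the same model without loss, and state the constant-rate assumption.

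The cost is one or two sentences and a slightly less favourable figure. Enrolment, design and analysis stay as they are.
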